## Discussion

The aim of our trial is to investigate the efficacy, acceptability, and feasibility of an intensive 1-week iCBT program for SAD compared to a waitlist control. To the best of our knowledge, this is the first RCT evaluating the efficacy of an intensive individually delivered 7-day iCBT treatment for any disorder including SAD. While our pilot trial [33] demonstrated preliminary evidence for the acceptability, feasibility, and positive outcomes of the intervention, including large reductions in social anxiety symptoms and functional impairment, the current study aims to extend these results using a more rigorous two-arm parallel-group RCT with follow-up.

The inclusion of a WLC group in this trial will allow for stronger conclusions to be made about treatment effects beyond external factors such as the passage of time, treatment expectancy, or clinician contact during the recruitment phase. The addition of clinician-rated measures and a diagnostic interview will enable us to assess the effects of the program on diagnoses of SAD and depression further to the self-report measures used in the pilot trial. Using validated clinical structured diagnostic interviews to assess SAD at baseline and follow-up will allow for stronger conclusions around intervention outcomes as they are less influenced by social desirability biases than self-report measures [93].

The study is strengthened by the inclusion of various outcome variables that explore the impact of the intervention beyond social anxiety symptoms, including on depression, quality of life, functional impairment, and personality traits and functioning. The inclusion of 1-month follow-up measures will also allow us to ascertain if treatment outcomes are sustained after the intensive 1-week treatment period.

The current study further extends the pilot trial as it is being completed outside of COVID-19 pandemic conditions. Significant increases in the use of online interventions for anxiety and depression were seen during the pandemic [94]. This study will allow us to ascertain whether the strong results and high levels of engagement found in the pilot trial are replicated in the current, post-pandemic period.

The inclusion of extensive qualitative open-ended questioning around participants’ experience of the treatment, with a direct focus on feedback around treatment satisfaction, side effects, treatment preferences, and suggestions for improvement, is a further strength of this study. The feasibility and acceptability of intensive iCBT is not well understood, and consequently, this qualitative data will help us to make evidence-based, patient-centred improvements to the treatment as needed before wider dissemination outside of research settings.

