### The current study

The proposed research will examine whether delivering iCBT in an intensive format over 1 week is effective in treating SAD symptoms relative to a waitlist control (WLC) group. A WLC condition was chosen as a comparator for several reasons. First, it provided a practical and feasible first step in evaluating the efficacy of this treatment, to determine whether a larger, more costly trial to compare it to an active treatment group or standard-paced CBT is warranted. WLC provided a clearer measure of treatment effects as it is more standardised than a usual care control group. Usual care control groups introduce more heterogeneity because participants receive varying levels and types of treatment. The WLC design also controlled for some factors such as the passage of time, the effects of repeated assessment, and regression to the mean which may have explained some improvements observed in the previous pilot trial. This study is the first RCT evaluating the efficacy of intensive, individual, online CBT for SAD. It is strengthened by the addition of follow-up assessment 1 month post-treatment and a clinician-rated diagnostic interview to assess the efficacy of the treatment beyond the self-report measures used in the pilot trial.

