### Control: waitlist control group

Participants allocated to the WLC group will be informed that they will be able to access the treatment after a waiting period of 6 weeks, during which they will complete three sets of online questionnaires. WLC participants will be sent automated emails via the REDCap platform with a link to complete questionnaires the day after their interview is completed (baseline, T1), 2 weeks later (T2), and 6 weeks post-baseline (T3). At T3, they will also be contacted to re-complete the telephone diagnostic interview, after which they will schedule the start date for their treatment week if they still choose to participate. WLC participants will follow the same procedure as the treatment group before (preparation call), and during their treatment week, receiving the treatment and clinician support over 1 week, and complete post-treatment questionnaires 1 week after completing their intervention. This post-treatment assessment will be used to assess WLC participants’ immediate treatment outcomes which will be included in the analysis of predictors of treatment outcome. The WLC will not be asked to complete any further follow-up assessments to minimise participant burden.

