### Blinding

Treatment group allocation will be concealed from the research team and applicant until it is determined an applicant meets inclusion criteria and is invited to participate in the study. Treatment group allocation cannot be concealed from the participants or the researchers during group allocation, as participants will be informed by the researchers when they can commence their treatment. Primary outcome data will be based on self-report assessment to protect from experimenter bias. It is not feasible to conduct blinded diagnostic interviews at follow-up due to funding constraints.

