### Trial outcomes and description of materials

After randomisation, all participants will complete a set of self-report questionnaires at baseline (T1), post-treatment (T2), and at 1-month follow-up (T3). Both groups will also be asked to complete a brief phone diagnostic interview [the ADIS MDD and SAD modules; [56]] at the 1-month follow-up (T3). Table 2 includes a list of assessment measures used and at which time point.

**Table 2 Tab2:** Materials used at each study time point

Questionnaire	Recruitment (T0)	Baseline (T1)	Post-treatment (T2)	One-month follow-up (T3)
Demographics	X			
Eligibility questions	X			
ADIS-5 modules	X			X
SPS	X	X	X	X
SIAS	X	X	X	X
PHQ-9	X	X	X	X
WSAS	X	X	X	X
LPFS-BF 2.0		X		X
PID-5-BF		X		X
HSU	X			
CEQ		X		
TSQ^a^			X	
Strategy use			X	X

^a^TSQ is completed by the treatment group only

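### The Discussion lists treatment expectancy among the factors the waitlist lets the trial see beyond, but in this open, self-rated trial only expectancy before allocation can be balanced

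*Protocol article*

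**What the plan says.** The Discussion of the protocol article says the waitlist group will "allow for stronger conclusions to be made about treatment effects beyond external factors such as the passage of time, treatment expectancy, or clinician contact". The sentence then ties the last item, contact with clinicians, to the recruitment phase.

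The Background (The current study) gives a shorter, openly partial list: the waitlist design "controlled for some factors such as the passage of time, the effects of repeated assessment, and regression to the mean". Expectancy is not on it.

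Three features of the design bear on the claim:

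- Blinding: "Treatment group allocation cannot be concealed from the participants or the researchers during group allocation". The same section makes the primary outcomes self-report, to guard against experimenter bias.
- Control: waitlist control group: these participants "will be informed that they will be able to access the treatment after a waiting period of 6 weeks".
- Primary outcome measures: both co-primaries, the SPS and the SIAS, are self-report scales.

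The limitations section names the passive control first. The consequence it draws is that other care cannot be controlled, and it leaves a digital placebo or psychoeducation control to future studies. It does not mention expectancy.

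**The concern.** A comparison supports conclusions beyond a given factor only if that factor acts equally in both arms. Here one arm knows it is being treated now, and the other knows it is waiting. Both then rate their own social anxiety at two weeks. Any improvement that comes from expecting to improve, or any lack of it that comes from expecting to wait, enters the difference between the arms.

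What is at stake is how the result is read. If the sentence carries over into the results paper, readers will be told that the design helps to set expectancy aside. In fact the estimate includes it. The limitations section does not correct this, because it never says that expectancy is uncontrolled.

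**Working it through.** **Step 1: the listed factors against the design.**

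| Factor | Alike in both arms? | Basis in the protocol article |
|---|---|---|
| Passage of time | Yes | Both arms assessed at 2 and 6 weeks post-baseline (Trial design and setting) |
| Repeated assessment | Yes, for the outcome scales | Same SPS, SIAS, PHQ-9 and WSAS schedule (Table 2) |
| Regression to the mean | Yes | Same entry thresholds, applied before randomisation (Eligibility criteria) |
| Clinician contact at recruitment | Yes | Randomisation follows the telephone interview (Randomisation and allocation procedures) |
| Expectancy before allocation | Yes, on average | Randomisation |
| Expectancy after allocation | No | Arm known; six-week wait announced; outcomes self-rated |

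Only the last row fails. Self-report protects against the experimenter's expectations, not the participant's.

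**Step 2: whether the planned measurements can rescue the claim.** The credibility and expectancy questionnaire (CEQ) is given at T1 (Table 2), and T1 comes after randomisation (Trial outcomes and description of materials). In the treated arm it also follows the preparation call (Intervention section). A CEQ difference between arms could therefore itself result from allocation. The questionnaire can describe expectancy but does not make the arms comparable on it.

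**Step 3: why the two parts cannot be separated.** Let *s* be the effect specific to the programme and *b* the shift due to differing expectancy after allocation, both in SD units. The trial estimates only *D = s + b*. No arm receives expectancy without the programme, so *s* and *b* cannot be told apart.

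**Step 4: the plan's sample size, used below.** Inputs from Sample size calculations: effect 0.92, alpha 0.05 (two-sided assumed), power 0.80. The normal approximation is *n* = 2(1.960 + 0.842)² / 0.92² = 18.5, so 19 per group. The exact two-sample t-test gives 19.55, so 20. The stated 20 is reproduced, and the point does not depend on it.

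**Step 5: an illustration of size.** The documents give no value for *b*, so the values here are assumptions. Set *s* = 0 and test one co-primary with a two-sample t-test at two-sided alpha 0.025 (Statistical analysis). The noncentrality is *b*√(n/2). For *b* = 0.40 it is 0.40 × √10 = 1.26 at 20 per group and 0.40 × √12.5 = 1.41 at 25 per group.

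| Assumed *b* (SD) | Chance of significance favouring iCBT, 20 per group | 25 per group |
|---|---|---|
| 0 | 1.25% | 1.25% |
| 0.10 | 2.7% | 2.9% |
| 0.40 | 15.4% | 19.4% |

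This is a simple t-test rather than the planned mixed model. It shows direction and rough scale only.

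**The case against.** The strongest reply is that the sentence is modest. It speaks of stronger conclusions, directly after describing a pilot that had no control group, and against that standard a waitlist is a real gain. This stands: a reader might infer that the protocol says the waitlist removes expectancy, and it does not.

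The qualifier about the recruitment phase may also be meant to cover expectancy. It reads most naturally as limiting clinician contact alone. Even on the wider reading it rescues only expectancy before allocation, and the sentence would still need to say so.

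Three other inferences are tempting and are not supported:

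- **That the Background and Discussion contradict each other.** The Background list is introduced as examples, so leaving expectancy out does not deny it.
- **That the follow-up diagnostic interviews cannot support stronger conclusions.** The Discussion says they "will allow for stronger conclusions around intervention outcomes as they are less influenced by social desirability biases than self-report measures". That is a comparative point about one bias. Lack of blinding is a different bias, and it is disclosed both under Blinding ("It is not feasible to conduct blinded diagnostic interviews at follow-up due to funding constraints") and in the limitations. The interviews also add diagnoses that the pilot lacked, and they take place at T3, so they do not touch the self-rated primary comparison at two weeks.
- **That the review effects in the Background measure expectancy.** Those are 0.79 in size against waitlist and 0.55 against controls overall, a gap of 0.79 − 0.55 = 0.24. The mix of controls behind 0.55 is not given and may include waitlist trials, and other differences contribute. The gap says nothing definite about expectancy.

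Finally, the passive control is openly named as a limitation and the trial is presented as a first step. That is fair, but the consequence for expectancy is still not stated.

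**Conclusion.** The point holds for one phrase. In an open waitlist trial with self-rated co-primary outcomes, expectancy after allocation differs between arms and is part of the estimate, so the design does not support conclusions beyond it. Expectancy before allocation is balanced by randomisation.

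This rests on the stated lack of concealment from participants, the announced wait and the self-report outcomes. It needs no assumption about how large expectancy effects are. Their size cannot be derived from the documents, and the range in the working is illustrative.

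Severity is minor. The issue is what the trial may conclude. Sample size, alpha, endpoints and analysis are unaffected.

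**What to change.** 1. In the Discussion sentence, delete treatment expectancy or limit it explicitly to expectancy before allocation.
2. In the limitations section, and in the interpretation section of the results paper, state that the estimate is the effect of the guided programme, including any expectancy effect, compared with waiting. Clinician guidance is part of the defined intervention and need not be listed as a separate distortion.
3. Optionally, repeat beside the Discussion sentence on interviews the caveat about unblinded assessors that already stands under Blinding and in the limitations.

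The cost is two or three sentences and a slightly more modest claim. The Trial status section says that data collection is complete and analysis under way, so the wording of the results paper is the natural place to apply it. No data or analysis need change.

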### Limitations of the study and future research

The results of this study should be interpreted with consideration of some limitations. Firstly, the use of a passive (waitlist) versus active control group means that while it is discouraged for participants to commence other therapies or medication during the waiting period, we are unable to control for other care they receive during this time. Future studies would benefit from comparing the treatment to an active control condition such as a digital placebo program or a psychoeducation control group. Future research should also compare this intervention to standard-paced iCBT or intensive face-to-face CBT. While our predictor analyses will provide some initial understanding as to whom this intensive approach is most suited, a RCT comparing the intensive and standard-paced formats (and to traditional face-to-face formats) will provide further clarification as to who benefits most from these diverse treatment approaches. A further limitation relates to the relatively short follow-up period; future studies would be strengthened by a longer-term follow-up period (e.g. 3 months or longer) to measure the longer-term impact of the intervention. In addition, our power calculations have been informed by meta-analyses of standard paced iCBT [92] and may have overestimated the expected between-group effect size. Future studies should consider using minimal important clinical differences to inform sample size calculations, to ensure similar studies are powered to detect changes that are not only statistically significant, but clinically meaningful.

Second, the risk of bias cannot be completely eliminated in the collection of some study data. It is not feasible to blind researchers to participant group allocation follow-up interviews. We will also rely on participant self-report to measure some engagement variables (length of time spent reading module material or practising skills) so this may be inaccurate. Relatedly, as the treatment is completed by participants online rather than in vivo with a clinician, it is not possible for clinicians to model the therapy skills (e.g. exposure). As such, it will be unclear if participants are implementing these skills with complete fidelity to the program instructions.

A further limitation relates to the generalisability of the results given that the sample of included participants will be self-referred and likely motivated to complete the trial. The results we obtain in this trial may not generalise to all individuals with SAD but rather to a subset who are interested, engaged, and motivated to try an intensive treatment approach. Future studies should test the generalisability and effectiveness of the program outcomes in a community sample, in routine-care settings, which tend to draw a more diverse and representative sample of participants including those with more severe and complex presentations [e.g. [95, 96]].

Finally, for reasons of feasibility, clinical support will be shared amongst the clinical team over a participants’ treatment week. It will be unclear whether this has an impact on participants during their treatment. If feasible, consistency in the clinician providing clinical support to each participant may be a consideration for future research trials.

## Conclusion

Intensive face-to-face CBT and iCBT have consistently demonstrated efficacy for improving symptoms of SAD. However, to the best of our knowledge, no studies have evaluated the efficacy of intensive individual iCBT for SAD delivered online. Intensive online treatments have the potential to help overcome barriers to accessing traditional face-to-face treatments by reducing costs, having immediate availability, and not relying on the regular and ongoing availability of trained clinicians, which is particularly valuable in rural and remote areas. If demonstrated to be effective, intensive iCBT for SAD may be a novel way to deliver treatment faster, with potential to reach more clients, and reduce drop-out rates. We believe it has great potential to provide rapid symptom improvement for individuals with SAD. Considering these potential benefits, investigating the efficacy of intensive iCBT for the treatment of SAD is an important area of future research and studies that adopt rigorous methodologies (including RCT with follow-up) are much needed.

## Trial status

This trial was registered with the Australian New Zealand Clinical Trials Registry on March 1, 2022 (ACTRN12622000361707). Trial recruitment began on March 18, 2024, and the first trial participant was enrolled on March 26, 2024. The trial protocol was submitted for publication in May 2024. Recruitment was completed in June 2024 and all data collection finalised by the end of July 2024, with analysis of results currently underway.

## Data Availability

After publication of the study results, de-identified data may be made available to other researchers upon reasonable request.

## Abbreviations

ADIS-5: Anxiety Disorders Interview Schedule for DSM-5
CBT: Cognitive behavioural therapy
CEQ: Credibility/Expectancy Questionnaire
iCBT: Online cognitive behavioural therapy
LPFS-BF 2.0: Level of Personality Functioning Scale—Brief Form 2.0
PHQ-9: Patient Health Questionnaire-9
PID-5-BF: Personality Inventory for DSM-5 Brief Form
SAD: Social anxiety disorder
SIAS: Social Interaction Anxiety Scale
SPS: Social Phobia Scale
TSQ: Treatment Satisfaction Questionnaire
WLC: Wait list control
WSAS: Work and Social Adjustment Scale
